Patients with SOT may benefit from a single dose of PCV7 followed by PPV23 12 months later. Children who have received PCV7 previously as part of the childhood immunization program might respond better if the PPV23 is given at least 12 month after the last dose of PCV7.

**Aims of the study:** The aim of this study is to compare the quantitative antibody responses of a sequential vaccination schedule of PPV23 with those of a sequential schedule of PCV7 followed by PPV23 12 months later in adult renal transplant recipients by measuring the concentrations of serotype-specific IgG in sera using an isotype-specific ELISA that has recently been recommended by the World Health Organization.

For a subset of subjects the T-cell mediated immune response will be evaluated in both groups.

**Study design:** randomized, double blind, controlled trial

**Methods:** Taking blood to quantify specific immunoglobulins und cellular immunity.

**Study drugs** *1. PPV23* (Pneumo 23®)

1. *PCV23* (Prevenar ®)

**Subjects:** A total of 78 renal transplant patients will

be enrolled into the study.

**Main outcome variable:** 1. Antibody concentrations after vaccination

- Fold increase of antibody response as compared to baseline 8 weeks after the vaccination

- Number of subjects with seroconversion defined as minimum 2-fold titer increase and a serum concentration of at least 1 µg/ml

- Number of subjects with at least > 2-fold increase for 2 of the 7 measured serotypes

2. For the subset of subjects included in the evaluation of cellular immunity

- T-cell response after each vaccination as determined by the frequency of cytokine producing T-cells induced by conjugated pneumococcal Ag

- Increase in frequency of cytokine producing T-cells induced by conjugated pneumococcal Ag after each vaccination as compared to baseline

.

**Statistics:** All patients will be included in the analysis as randomised.

Although the primary endpoint is the difference in antibody concentration as continuous variable between study groups we base our sample size calculation on the more conservative but clinically more useful binary variable vaccine response. A vaccine response by ELISA will be defined as a > 2 fold increase in prevaccination titer and an absolute postvaccination value of at least 1 µg/ml.

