**Aim of the study**

The aim of this study is to compare the quantitative antibody responses of PPV23 with those of a sequential schedule of PCV7 followed by PPV23 12 months later in adult renal transplant recipients by measuring the concentrations of serotype-specific IgG in sera using an isotype-specific ELISA that has recently been recommended by the World Health Organization.

For a subset of subjects the T-cell mediated immune response will be evaluated in both groups.

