Although the primary endpoint is the difference in antibody concentration as continuous variable between study groups we base our sample size calculation on the more conservative but clinically more useful binary variable vaccine response. A vaccine response by ELISA will be defined as a > 2 fold increase in prevaccination titer and an absolute postvaccination value of at least 1 µg/ml.

The study is powered to detect an improvement in vaccine response with the conjugate vaccine in any of the 7 serotypes. The study is set to yield a power of 80% at a significance level of 5% to detect a 35% improvement in the response rate for a given serotype. The response rate in the control group is expected at about 45%. Thus the calculated sample size will be 35 in each group. We added 10% to adjust for potential loss-to-follow-up which results in 39 patients in each group.

We expect antibodies being log-normally distributed. Geometric mean antibody concentrations (GMCs) for each pneumococcal serotype will be compared between the two groups by using the 2-tailed, unpaired Students’s t-test after log transformation of the raw data, given our distributional assumptions hold.

For binary variables we will calculate risk ratios and exact 95% confidence intervals. Vaccination efficacy (Ev) will be calculated as: Ev = (1-RR) x 100. For hypothesis testing we will use the Fisher’s exact test.

All analysis will be conducted by using a 2-sided p value with a type I error rate of < 0.05.

*Determination of serum antibodies against vaccination antigens:*

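### Seven serotypes are each tested at an unadjusted two-sided 5% with no primary visit named, and the 80% power applies to one given serotype, not to any of the seven

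*Protocol*

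**What the plan says.** All of this stands in the protocol itself.

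- **Endpoint and tests.** Under Definitions and statistical methods (Materials and Methods), the primary endpoint is the between-group difference in antibody concentration as a continuous variable. Geometric means are compared by t-test on the log scale for each serotype. Binary response (more than a 2-fold rise and at least 1 µg/ml) is tested with Fisher's exact test. No primary serotype or composite is named.
- **Error level.** "All analysis will be conducted by using a 2-sided p value with a type I error rate of < 0.05".
- **Power.** "The study is powered to detect an improvement in vaccine response with the conjugate vaccine in any of the 7 serotypes". The next sentence sets "power of 80% at a significance level of 5% to detect a 35% improvement in the response rate for a given serotype". The planning values follow: "The response rate in the control group is expected at about 45"%, "Thus the calculated sample size will be 35 in each group", and "We added 10% to adjust for potential loss-to-follow-up which results in 39 patients in each group".
- **Visits.** The Schedule of events has post-vaccination serology at Day 56 and Day 421. The endpoint list speaks of concentrations after vaccination, and of fold increase at 8 weeks, without saying which vaccination.
- **Aims.** The Study synopsis compares "a sequential vaccination schedule of PPV23 with those of a sequential schedule of PCV7 followed by PPV23 12 months later". The Aim of the study section says the trial will "compare the quantitative antibody responses of PPV23 with those of a sequential schedule of PCV7 followed by PPV23 12 months later".

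**The concern.** Seven tests, each at 5%, do not together keep a 5% error rate for the conclusion that priming with the conjugate vaccine is better. The only hint of what would count as a positive result is the powering sentence, which speaks of any of the seven serotypes. With two post-vaccination serology visits and none primary, the visit can also be chosen after the results are seen.

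The visit matters for content too. At Day 56 each patient has had one dose, so a difference there says nothing about the sequential schedules in the title. The protocol's own background already cites a randomised comparison of the two single vaccines in kidney recipients at 8 weeks. What is new here is the result after the second dose, and the protocol does not make it primary.

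**Working it through.** **1. The plan's own sample size.** Inputs from the protocol: 45% in controls, a 35-point gain (so 80%), two-sided 5%, 80% power.

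n = [1.960·√(2·0.625·0.375) + 0.842·√(0.45·0.55 + 0.80·0.20)]² / 0.35² = 28.8, that is 29 per group.

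With continuity correction: n′ = (28.83/4)·[1 + √(1 + 4/(28.83·0.35))]² = 34.3, that is 35 per group. Then 35/0.9 = 38.9, that is 39 per group. Both stated figures reproduce. A relative 35% gain (45% to 60.75%) would need 157–169 per group, so the gain is absolute. The calculation is for one serotype at one comparison.

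**2. Power at 35 per group, 45% vs 80%, exact Fisher.**

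| Level | Power per serotype |
|---|---|
| 0.05 | 82% |
| 0.05/7 = 0.00714 | 57% |

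**3. False positives with no true difference.** For independent tests at 5%, the chance of at least one is 1 − 0.95⁷ = 30.2% at one visit and 1 − 0.95¹⁴ = 51.2% over both. Serotypes and visits will be correlated, and the protocol gives no correlation. The table is from simulation at 35 per group, with an equal correlation among serotypes assumed at 0, 0.5 or 0.8. The two-visit column assumes between-visit correlations from 0 to 0.8.

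| t-tests on log IgG, assumed serotype correlation | One visit, either direction | One visit, favouring conjugate only | Either visit, either direction |
|---|---|---|---|
| 0 | 30% | 16% | up to 51% |
| 0.5 | 23% | 12% | 34–41% |
| 0.8 | 15% | 7–8% | 22–28% |

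The nominal level is 5% for the two-sided columns and 2.5% for the one-direction column.

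**4. The binary response.** Fisher's test is conservative. At a 45% response rate and 35 per group its true two-sided size is 2.5%. Seven independent tests give 1 − (1 − 0.0252)⁷ = 16%. Simulation gives about 15% at serotype correlation 0.5 and 11–12% at 0.8. Counting only results that favour the conjugate vaccine, the figure is about 6–9%.

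**5. The aims.** One aim compares two-dose schedules. The other sets PPV23, with no second dose mentioned, against a two-dose schedule. The table of regimens fixes the control arm as PPV23 followed by PPV23, so the design is clear, but neither aim states the visit.

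**The case against.** - **There is no written success rule.** A reader might infer that the protocol declares success on any one significant serotype, or that it specifies 14 primary tests. It does neither. The any-of-seven phrase is a powering statement, and the visits are never called co-primary. The phrase can also be read as meaning that power is 80% whichever serotype is considered, in which case the two power sentences agree. This stands, and it is why the false-positive figures are conditional on one significant serotype being read as benefit. The ambiguity remains.
- **The largest figures do not fit every reading.** A reader might take 30% and 51% as the error rate. They need independent tests and count differences in either direction, whereas the powering sentence concerns improvement in a binary response. This stands. The lower figures in the working apply there, and they too exceed the nominal level.
- **Power is not short as planned.** With unadjusted tests, the chance of at least one significant serotype is no lower than the single-serotype power if that effect is real. The 57% arises only once alpha is split. This stands.
- **The title and aims point to the visit after dose 2.** They do, but the endpoint and statistics text never fixes it.
- **Adjustment can be left to the statistical analysis plan.** Often so. Here the protocol sets 5% for every analysis and gives no sign of a family-wise rule, and the primary visit and the target of the power statement belong in the protocol.
- **Power for the continuous endpoint might be read off the response rates.** A reader might convert 45% vs 80% into a shift in log IgG. The documents do not support that: response combines a fold rise with a threshold, and no standard deviation is stated.

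**Conclusion.** The point holds. Followed as written, the protocol does not keep its stated error rate below 5% for an overall conclusion drawn from whichever serotype turns out significant. At one visit the risk is about 15–30% for two-sided t-tests, about 7–16% for t-test results favouring the conjugate vaccine (against 2.5%), and about 15–16% for two-sided Fisher tests (11–12% at serotype correlation 0.8). Over either visit it is about 22–51% for two-sided t-tests. These ranges rest on assumed correlations of 0 to 0.8 and on 35 evaluable patients per group.

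The 80% power is correctly calculated, but for one serotype at an unadjusted 5%. It does not cover a family-wise controlled claim about any of the seven. The missing primary visit adds to the error and leaves open whether the trial answers a single-dose or a sequential-schedule question. The mismatch between the two aim statements is minor by itself.

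**What to change.** - **One primary comparison.** Log IgG at Visit 4 (Day 421), PPV23–PPV23 versus PCV7–PPV23. Use either Holm over the seven serotypes at family-wise two-sided 5%, or a single test on each patient's mean log IgG over the seven serotypes, with single serotypes secondary.
- **Day 56.** Make it secondary.
- **Aim of the study.** Word it as in the synopsis, with both arms as sequential schedules.
- **Power statement.** Replace the any-of-seven wording. Say that 35 per group gives about 80% power (82% by exact Fisher) for one prespecified serotype at unadjusted 5%, and about 57% per serotype for the responder endpoint at 0.05/7.
- **Continuous endpoint.** State no power for log IgG unless a standard deviation and a shift are given as assumptions.

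These are changes of wording and no extra patients are proposed, but there is a cost in power. Under Holm, the first step for the responder endpoint falls from 82% to 57% per serotype; keeping 80% at 0.05/7 would need about 52 per group, or 58 with 10% loss. The single composite test avoids splitting alpha, at the price of moving serotype-level claims to secondary status.

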The administrator of the vaccine and the patient will be blinded to the type of vaccine given.

Patients randomized to group A will receive the PPV23 vaccine as early as 6 months after transplantation and the second dose of PPV23 12 months after the first vaccination.

Patients randomized to group B will receive the first PCV7 as early as 6 months after transplantation, followed by a PPV23 dose 12 months after the PCV7.

|  | 6 M after Tx | 18 M after Tx |
| --- | --- | --- |
| Regime 1 | PPV23 | PPV23 |
| Regime 2 | PCV7 | PPV23 |

*Study endpoints:*

Immunogenicity:

- Antibody concentrations after vaccination
- Fold increase of antibody response as compared to baseline 8 weeks after the vaccination
- Number of subjects with seroconversion defined as minimum 2-fold titer increase and a serum concentration of at least 1 µg/ml
- Number of subjects with at least > 2-fold increase for 2 of the 7 measured serotypes

For the subset of subjects included in the evaluation of cellular immunity

- T-cell response after each vaccination as determined by the frequency of cytokine producing T-cells induced by conjugated pneumococcal Ag
- Increase in frequency of cytokine producing T-cells induced by conjugated pneumococcal Ag after each vaccination as compared to baseline

*Safety data:*

Patients will be instructed to record local reactions /e.g. redness, swelling, and tenderness) and systemic reactions (e.g. fever, nausea, and vomiting).

At the time of vaccination, medical providers will be asked to record appearance of local reactions occurring within 30 minutes of injection. At the time of each vaccination visit patients will be given a diary card, thermometer and a measuring tape. On postvaccination days 1 through 3 patients will be asked to record presence or absence of redness and swelling (in millimetres), pain/tenderness (graded none, mild, moderate or severe), loss of appetite, vomiting, headache, fussiness, increased sleep or other potential adverse reactions. Data from the diary will be recorded as well as changes in medications or medical care.

Serum samples will be obtained immediately before, 8 weeks the first and the second vaccination.

In a subgroup of patients in each treatment regimen blood for cellular response will be taken immediately before vaccination and 7-10 days after vaccinations.

*Definitions and statistical methods:*

All patients will be included in the analysis as randomised.

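### The primary comparison of serotype-specific IgG is an unpaired t-test that leaves out the scheduled pre-vaccination concentration; it is valid but gives up precision that baseline adjustment would recover at negligible cost

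*Protocol*

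**What the plan says.** In the Protocol, Materials and Methods, *Definitions and statistical methods*, "the primary endpoint is the difference in antibody concentration as continuous variable between study groups". The endpoint list gives this as "Antibody concentrations after vaccination", separately from "Fold increase of antibody response as compared to baseline 8 weeks after the vaccination".

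The only test named for the continuous concentrations is this: "Geometric mean antibody concentrations (GMCs) for each pneumococcal serotype will be compared between the two groups by using the 2-tailed, unpaired" Student's t-test, after log transformation and provided that the distributional assumption holds ("We expect antibodies being log-normally distributed"). The synopsis says the same under *Statistics*. Neither place mentions a covariate. On error rate: "All analysis will be conducted by using a 2-sided p value with a type I error rate of < 0.05".

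On sampling: "Serum samples will be obtained immediately before, 8 weeks the first and the second vaccination". The *Schedule of events* shows a serology draw at Visit 1, Day 56, Day 365 and Day 421. Only the draw for cellular immunity is restricted to a subgroup, so a Visit 1 concentration of each of the seven serotypes is planned for every patient.

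**The concern.** Patients will not start from the same antibody level. The exclusion criteria bar pneumococcal vaccination only within the preceding 5 years, so earlier vaccinees may enter. The protocol itself treats the starting level as informative, because its fold-increase and responder endpoints are defined against it. The primary continuous comparison alone does not use it.

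If baseline predicts the post-vaccination level, an unadjusted comparison has a wider standard error than it needs. Any difference in baseline means that randomisation happens to produce is also carried, in part, into the estimated GMC ratio. With 35 evaluable patients per arm, such differences are not small. What is at stake is power and the stability of the estimate, not the validity of the test.

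**Working it through.** **Inputs from the protocol** (*Definitions and statistical methods*): control response 45%; improvement 35%; two-sided 5%; power 80%; 35 per group, raised to 39 for 10% loss. **Assumed:** rho, over a range from 0 to 0.7. The protocol gives neither rho nor the SD of log IgG, so differences are in SD units of log post-vaccination IgG.

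**1. The plan's own sample size.** With 45% versus 80%, the mean proportion is 0.625.

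n = [1.96 × √(2 × 0.625 × 0.375) + 0.8416 × √(0.45 × 0.55 + 0.80 × 0.20)]² / 0.35² = (1.342 + 0.537)² / 0.1225 = 28.8, so 29.

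With continuity correction: (28.8/4) × [1 + √(1 + 4/(28.8 × 0.35))]² = 34.3, so **35**. Then 35/0.9 = 38.9, so **39**. Both stated figures are reproduced. The working number for the analysis is therefore 35 evaluable per arm.

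**2. What the t-test can detect.** Its standard error is √(2/35) = 0.239 SD on 68 degrees of freedom. The noncentral t distribution gives 80% power at a difference of 0.68 SD (0.679).

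**3. The same difference with log baseline as covariate.** The standard error becomes 0.239 × √(1 − rho²) × √(1 + 1/66), on 67 degrees of freedom. The last factor is the small-sample price of estimating the slope. The fourth column is 35/(1 − rho²), the per-arm size at which the t-test would be equally precise.

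| Assumed rho | ANCOVA power at 0.68 SD | Difference with 80% power | t-test n per arm to match |
|---|---|---|---|
| 0 | 79.4% | 0.685 SD | 35 |
| 0.3 | 83% | 0.65 SD | 38 |
| 0.5 | 89% | 0.59 SD | 47 |
| 0.7 | 97% | 0.49 SD | 69 |

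Simulation with 5,000 trials per setting agrees. At 0.68 SD the rejection rates for t-test and ANCOVA were 80.1% and 82.6% (rho 0.3), 80.7% and 89.6% (rho 0.5), and 79.6% and 97.2% (rho 0.7). With no true difference, both stayed at about 5%.

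**4. Chance imbalance.** The difference in baseline means also has an SD of √(2/35) = 0.239 baseline SDs. For one serotype it exceeds 0.25 SD in either direction with probability 30%. The t-test estimate carries rho times the imbalance. A one-SD imbalance (0.239) therefore shifts it by 0.07, 0.12 or 0.17 SD at rho 0.3, 0.5 or 0.7. In simulated trials with rho 0.5, a true difference of 0.68 SD and an imbalance above 0.24 SD, the mean t-test estimate was 0.86 and the mean ANCOVA estimate 0.68. Over all randomisations both averaged 0.68.

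**5. Does the fold-increase endpoint already do this?** With equal SDs before and after, comparing log fold increases has variance factor 2(1 − rho), against 1 for the t-test and 1 − rho² for ANCOVA. At rho 0.3 these are 1.40, 1 and 0.91; at rho 0.5 they are 1.00, 1 and 0.75; at rho 0.7 they are 0.60, 1 and 0.51. Apart from the small-sample factor in step 3, the change score is never better than ANCOVA, and below rho 0.5 it is worse than the unadjusted t-test.

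**The case against.** The strongest reply is that nothing here is an error. The t-test holds its level and is unbiased over randomisations, and its standard error already allows for chance imbalance. Baseline is not ignored in the trial as a whole, since fold increase and the responder endpoints refer to it. The benefit depends entirely on a rho that the protocol does not give. That rho could be low, particularly if the comparison is made after the second vaccination, some 14 months from Visit 1. The protocol's own background also says that antibody falls substantially within 2 years of vaccination, which weakens old vaccination as a source of baseline spread.

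All of this stands as a limit on the size of the point. It does not remove it. The worst case for adjustment, rho near zero, costs less than one percentage point of power, and the fold-increase endpoint is no substitute.

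A reader might infer stronger claims that the documents do not support:

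- **That the t-test is at fault for excluding randomised patients**, given "All patients will be included in the analysis as randomised". A t-test does need a post-vaccination value, but so does ANCOVA at a single visit, so leaving out baseline is not the cause. The sentence can be read as analysis by assigned group, and rules for missing sera may sit in an analysis plan that is not shown.
- **That a serious imbalance in some serotype is near certain.** This depends on the threshold. At the 95% limit for one serotype (1.96 × 0.239 = 0.47 SD), the chance for at least one of seven is 1 − 0.95⁷ = 30% if serotypes are independent, and less if they are positively correlated.
- **That adjustment narrows every confidence interval.** It does so on average when rho is more than slight. In simulation with 35 per arm, the ANCOVA standard error was the larger one in about 79% of trials at rho 0, 37% at 0.2 and 14% at 0.3, and almost never at 0.5.
- **That the imbalance can be set against a planned effect in SD units.** The protocol plans on a binary response and states no such effect.
- **That Day 421 is the primary visit.** The endpoint list says 8 weeks after vaccination without saying which one.

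**Conclusion.** The point holds as one of efficiency and of robustness to chance imbalance. The protocol itself fixes an unadjusted test for its primary endpoint while scheduling the measurement that would sharpen it. With 35 evaluable per arm and normal log concentrations, at the difference where the t-test has 80% power, adjustment changes power by about −1, +3, +9 and +17 percentage points at rho 0, 0.3, 0.5 and 0.7. The gain is therefore modest at rho 0.3 and large from 0.5 upwards. Where the true value lies cannot be settled from the protocol. The planned test is not invalid, and the change is advisable because the possible gain far outweighs the possible loss.

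**What to change.** In *Definitions and statistical methods* and in the synopsis, replace the t-test as the primary comparison. For each serotype, fit a linear model of log post-vaccination IgG on randomised group with log Visit 1 IgG of the same serotype as covariate. Report the adjusted GMC ratio with its 95% CI, and keep the unadjusted t-test as a sensitivity analysis.

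Use the Visit 1 sample as covariate whichever post-vaccination visit is primary. The Day 365 sample is taken after the randomised first dose and should not take its place. A longitudinal model over all serology visits is an option but is not needed for this point.

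The cost is a change of wording, one degree of freedom, and a loss of under one percentage point of power if rho is near zero. No extra serum, visit or patient is required.

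### Vaccination efficacy is defined as (1-RR) x 100, but every binary immunogenicity endpoint is a favourable event: on the usual reading a PCV7 advantage gives a negative value, and on no reading is it efficacy

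*Protocol*

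**What the plan says.** The statistical text stands twice in the protocol with the same content: in the Study synopsis under Statistics, and in Materials and Methods under Definitions and statistical methods.

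- Effect measure: "For binary variables we will calculate risk ratios and exact 95% confidence intervals".
- Derived measure, in the next sentence: "Vaccination efficacy (Ev) will be calculated as: Ev = (1-RR) x 100". Because of its position, the RR in this formula is the risk ratio of the binary variables.
- Binary variable used for the sample size: "A vaccine response by ELISA will be defined as a > 2 fold increase in prevaccination titer", together with a post-vaccination concentration of at least 1 µg/ml.
- Binary variables under Study endpoints: "Number of subjects with seroconversion defined as minimum 2-fold titer increase and a serum concentration of at least 1 µg/ml" and "Number of subjects with at least > 2-fold increase for 2 of the 7 measured serotypes".
- Expected direction: "The study is powered to detect an improvement in vaccine response with the conjugate vaccine in any of the 7 serotypes". The control response rate is put at about 45%, and the improvement to be detected at 35%.

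Under Study design and vaccines, group A receives PPV23 twice and group B receives PCV7 followed by PPV23, so there is no unvaccinated arm. No pneumococcal infection or disease outcome appears among the endpoints. Neither the event counted in the risk ratio nor the arm in the numerator is stated.

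**The concern.** The formula is borrowed from trials that count disease. There a good vaccine lowers the risk, RR falls below 1, and 1-RR is the share of cases prevented. Here the listed events are successes. If the risk ratio is taken in the ordinary way, on the event as defined and with the experimental arm over the control arm, a better conjugate arm pushes RR above 1 and Ev below zero. The result the trial is designed to find would then be reported as a negative vaccination efficacy.

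The label is a second problem that does not depend on the sign. The trial compares antibody responses between two active schedules. A positive percentage under the name vaccination efficacy would suggest protection against pneumococcal disease, which the trial does not measure. Readers could be misled, because the protocol's introduction describes renal transplant recipients as having a risk of invasive disease more than 60 times that of the general population.

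**Working it through.** **Inputs** (Definitions and statistical methods): control response p_A about 0.45; improvement 35%; power 80%; two-sided 5%; 35 per group, 39 after allowing 10% for loss to follow-up. The protocol states no Ev value, so the planning rates must be fixed first and Ev evaluated at them.

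**Step 1. Which response rate is planned in the conjugate arm?** The 35% could be absolute (0.45 + 0.35 = 0.80) or relative (0.45 x 1.35 = 0.6075). The stated sample size settles it.

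Two-proportion formula, with d = p_B - p_A and p̄ the mean rate:

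n = [1.96 √(2 p̄(1-p̄)) + 0.8416 √(p_A(1-p_A) + p_B(1-p_B))]² / d²

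- Absolute reading: p̄ = 0.625 and d = 0.35. n = [1.96 x 0.6847 + 0.8416 x 0.6384]² / 0.1225 = 28.8, so 29.
- With continuity correction: n' = (28.8/4) x [1 + √(1 + 4/(28.8 x 0.35))]² = 34.3, so 35. This is the protocol's figure, and 35/0.9 = 38.9 gives its 39.
- Relative reading: 157 per group, or 169 with continuity correction. Neither matches.

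The planning rates are therefore 45% and 80%.

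**Step 2. Ev at those rates, under each way of filling in what the protocol leaves open.**

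| Event | Ratio | RR | Ev = (1-RR) x 100 |
|---|---|---|---|
| Response | PCV7-PPV23 / PPV23-PPV23 | 0.80/0.45 = 1.778 | -77.8% |
| Response | PPV23-PPV23 / PCV7-PPV23 | 0.45/0.80 = 0.5625 | +43.8% |
| Non-response | PCV7-PPV23 / PPV23-PPV23 | 0.20/0.55 = 0.364 | +63.6% |

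The first row is the usual reading: the event as the endpoints define it, experimental arm over control.

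**Step 3. Does the sign depend on the planning values?** On the first-row reading, Ev < 0 exactly when RR > 1, that is, whenever p_B > p_A. So every PCV7 advantage in response gives a negative Ev. With the relative reading of the 35%, which does not reproduce the sample size, RR = 0.6075/0.45 = 1.35 and Ev = -35%. The size changes and the sign does not.

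**Step 4. What uses Ev?** The primary endpoint is antibody concentration as a continuous variable, compared by t-test on the log scale. Binary hypotheses are tested with Fisher's exact test. The sample size comes from the two response rates. The risk ratio and its exact interval are reported in their own right. None of these uses Ev.

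**The case against.** The strongest defence is that the protocol does not fix the sign. It names no event and no numerator arm, and a coherent reading exists. Risk and 1-RR sit naturally with an unfavourable event, and the authors' own table of earlier data in asplenic patients (Introduction) counts patients whose antibody response was lower than two-fold. Taken on non-response, 1-RR is a proper proportional reduction in vaccine failure, +64% at the planning rates. Event coding and arm order for a secondary summary are also often left to a statistical analysis plan, which may exist. And 1-RR does not strictly need an unvaccinated comparator, since it can be computed between two active schedules.

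Much of this stands, and it rules out three stronger readings that a reader might infer:

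- *The trial will necessarily report the wrong sign.* The document does not support this. The negative value depends on the usual response ratio, which the protocol does not spell out.
- *The plan yields three contradictory efficacies.* It does not. The three figures are one pair of rates under three definitions, and the protocol does not prescribe all three.
- *The trial's main inference is compromised.* It is not, because no test and no sample-size figure depends on Ev.

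The defence does not rescue the sentence. Nothing in the statistical section says that non-response is meant: the defined binary variable is response, and the stated aim is to improve it. Nor is the point merely about detail left for later. A formula is stated, twice, that does not suit the endpoints it follows. Defining the event and arm order would repair the sign but not the name: a relative reduction in antibody non-response is not vaccination efficacy. Applying Ev to local or systemic reactions does not help either, because fewer reactions are not efficacy.

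**Conclusion.** The point holds as an error in a secondary summary measure that should be fixed. Set against the listed endpoints, the Ev formula does not measure efficacy under any definition of its inputs. On the usual reading it turns the planned benefit (45% versus 80%, RR = 1.78) into Ev = -78%.

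The size rests on two assumptions. The first is that the 35% improvement is in percentage points, which is the reading that reproduces 35 per group. The second is that RR is the response ratio of PCV7-PPV23 over PPV23-PPV23, which is conventional but not stated. The mismatch between formula, label and endpoints rests on neither. The error is confined to how the binary results are summarised and described.

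**What to change.** Delete the Ev sentence in both places. In its place, for each binary immunogenicity endpoint, report:

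- the responder rate in each arm;
- the risk ratio with its direction stated (PCV7-PPV23 over PPV23-PPV23, values above 1 favouring PCV7), with the exact 95% confidence interval already planned;
- the risk difference with a 95% confidence interval.

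If a 1-RR measure is to be kept, define it on non-response with PCV7-PPV23 as the numerator, and call it the relative reduction in non-response rather than vaccination efficacy.

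The cost is two deleted sentences and one replacement line in each place, settled before analysis. Design, sample size, data collection and hypothesis tests stay as they are.
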